The current paper describes the protocol of the PRISMA study (pediatric research on improving speed, memory, and attention); a randomized controlled double-blind trial, approved by the medical ethical committee of the Academic Medical Centre in Amsterdam. The primary aim of the PRISMA study is to investigate the efficacy of neurofeedback for improving neurocognitive functioning after treatment for a pediatric brain tumor. Secondary, we hypothesize that subsequent to the expected neurocognitive changes achieved with neurofeedback, children will experience improved psychosocial functioning [25]. Neurocognitive functioning will be investigated by tests administered to the patient. Psychosocial functioning will be measured using patient-reported as well as caregiver and teacher reported questionnaires. Assessments will take place pre and post training, as well as six months post training, in order to examine the long-term effects of the training. Comparing the effects of neurofeedback to placebo feedback will assess efficacy of neurofeedback. Pre training results obtained with the brain tumor survivors will be compared to a control group of healthy siblings, to assess the level of dysfunction on the measures used in this study.

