### Statistical analyses

Intention-to-treat analyses will be conducted. Because of possible withdrawal before treatment starts, dropouts during the study, failure to fill out questionnaires, or research procedure violations, missing data will occur. Imputation of missing values will be carried out as much as possible to make intention-to-treat analyses feasible. Missing data will be imputed using Imputation and Variance Estimation Software [46].

Prior to the training (T0) we will assess differences between patients and siblings on neurocognitive and psychosocial functioning, using mixed modelling. Subsequently, we will conduct multivariate analysis of variance (MANOVA) to determine the effect of neurofeedback post-treatment (T1) on the primary and secondary outcomes, comparing the patients in the neurofeedback group to the patients in the placebo group. To control for possible differences in neurocognitive functioning prior to the training, T0 data will be included in the model as covariate. Finally, we will use repeated measures analysis for group (neurofeedback and placebo) x time (T0, T1, and six months follow-up, T2) to investigate the changes over time. To examine the possible effects of patient characteristics on the efficacy of the neurofeedback, the following variables will be assessed as covariates in the MANOVA and repeated measures analyses: age at assessment, age at diagnosis, diagnosis, time since diagnosis, and treatment modalities. All analyses will be conducted using SPSS. A *P*-value <0.05 will be considered significant.

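### The only analysis using the six-month data is a group x time test over T0, T1 and T2, which can be significant when the effect has gone by T2

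*Protocol article*

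**What the plan says.** The Background section states why patients are assessed again six months after training: "in order to examine the long-term effects of the training". It also says that efficacy is judged by comparing neurofeedback with placebo feedback.

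The Statistical analyses section plans two comparisons of the randomised arms:

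- **At T1:** "multivariate analysis of variance (MANOVA) to determine the effect of neurofeedback post-treatment (T1) on the primary and secondary outcomes". For this model, "T0 data will be included in the model as covariate".
- **Over all three visits:** a repeated measures analysis that crosses the two arms with "time (T0, T1, and six months follow-up, T2) to investigate the changes over time".

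Only the second uses T2. T0 is one of its three outcome levels. The covariates named for both models are patient characteristics: "age at assessment, age at diagnosis, diagnosis, time since diagnosis, and treatment modalities". The text names no T2 difference between arms, no T0-to-T2 contrast and no rule for what follows a significant interaction. The Power calculation section concerns the change from T0 to T1; T2 is not powered.

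**The concern.** The long-term question is whether the arms still differ at six months. A group x time interaction over three visits asks something else: whether the difference between arms is the same at T0, T1 and T2. Randomisation makes the expected difference at T0 zero, so a difference at T1 alone is enough to break that equality, whatever happens at T2. The test also has no direction.

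If this interaction is the evidence offered on long-term effect, a benefit present only at the end of training could be reported as one that lasts. Looking at the means afterwards would help, but the article states no rule for doing so, and there are many neurocognitive and questionnaire outcomes (Table 1).

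**Working it through.** **Inputs.** From the Power calculation section: 35 per arm, effect size 0.6, one-sided alpha 0.05, power 0.80. From Statistical analyses: two groups, three time levels, significance at P < 0.05. Assumed, because the article does not give them: SD 1 at each visit, the same correlation rho between every pair of visits (0.3 to 0.8), no dropout, and a two-sided 0.05 level for the T2 contrast.

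**Step 1: the plan's own figure.** The normal approximation gives n = 2 × (1.645 + 0.842)² / 0.6² = 34.3, so 35 per arm. The stated size reproduces.

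**Step 2: what drives the interaction test.** Let e be the difference between arms at (T0, T1, T2). The noncentrality is

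lambda = (n/2) × Σ(e_t − mean e)² / (1 − rho), on 2 and 2 × (70 − 2) = 136 degrees of freedom.

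- Vanished effect, e = (0, 0.6, 0): the mean is 0.2 and the sum of squares is 0.04 + 0.16 + 0.04 = 0.24.
- Sustained effect, e = (0, 0.6, 0.6): the mean is 0.4 and the sum of squares is 0.16 + 0.04 + 0.04 = 0.24.
- Late effect only, e = (0, 0, 0.6): again 0.24.

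So lambda = 17.5 × 0.24 / (1 − rho) = 4.2 / (1 − rho) in all three cases. Under these assumptions the test has exactly the same chance of significance for a vanished effect as for a sustained one.

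**Step 3: the alternative.** An ANCOVA of T2 on T0 has noncentrality d × √(n/2) / √(1 − rho²) on 67 degrees of freedom, where d is the difference at T2. With d = 0.6 the numerator is 0.6 × √17.5 = 2.51.

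**Step 4: results, probability of significance.**

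| rho | lambda | Interaction, vanished or sustained | T2 ANCOVA, vanished (simulated) | T2 ANCOVA, sustained: formula (simulated) |
|---|---|---|---|---|
| 0.3 | 6.0 | 57% | 4.9% | 74% (72%) |
| 0.5 | 8.4 | 73% | 4.9% | 82% (81%) |
| 0.7 | 14.0 | 92% | 4.7% | 93% (93%) |
| 0.8 | 21.0 | 99% | 4.9% | 98% (98%) |

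Simulation with 20,000 trials per setting agrees with the interaction column to within about one percentage point. With no effect at any visit, both tests reject in about 5%. The multivariate form of the interaction test is within about one point of the figures shown.

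**Step 5: sensitivity.** For a vanished effect of 0.5, the low end of the article's expected range, the interaction is significant in 42% to 93% of trials as rho goes from 0.3 to 0.8. For 0.8, the high end, it is 83% to nearly 100%. For a sustained effect of 0.6, the two tests are level at rho 0.75 (96.1% for the interaction, 96.2% for the ANCOVA), and the order reverses slightly at 0.8 (98.7% against 98.5%).

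**The case against.** The strongest reply is that the article fixes a model and not a decision rule. It does not use the word omnibus, and it does not say that a significant interaction will be taken as proof of lasting benefit. Contrasts for single visits can be drawn from the same model, and a fuller protocol or analysis plan, not shown here, may name them. This stands in part. A reader might infer that no T2 comparison is planned at all, or that a false claim of durability is built in. The document supports neither; it shows only that none is named here. What remains is that the article states which analysis uses T2, and that analysis, in its usual form, does not fit the purpose given for the visit.

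A second reply is that treating T0 as a response is not an error. That is correct: in a randomised trial both forms give valid comparisons between arms, and different models can serve different questions. The change in the role of T0 between the T1 and T2 analyses is a reason to align them, not a flaw in itself.

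A third reply concerns power. It would be tempting to say that the interaction test always has less power for a lasting effect. Step 5 shows otherwise: the T0-adjusted contrast gains at low to moderate correlation only, and has no advantage from about 0.75 upward.

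Finally, the follow-up question is not the one the trial was sized for, and T1 has its own baseline-adjusted analysis. This also stands.

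**Conclusion.** The point holds in a limited form. The six-month objective is paired with an analysis whose standard test can be significant when the T1 effect has vanished by T2: in about 57% to 99% of trials at an effect of 0.6, depending on the correlation. It is as likely to be significant then as when the effect is fully sustained. A T0-adjusted T2 contrast stays at about 5% when there is no T2 effect. For a sustained effect it also has more power at low to moderate correlation (about 73% against 57% at 0.3, and 81% against 73% at 0.5).

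The figures rest on equal variances, equal correlations, complete data and reading the analysis as the 2-degree-of-freedom interaction test. The correlations are assumed. The main argument is interpretability, which holds at every correlation examined; the power gain is secondary. It would go too far to say that a vanished effect will make the test significant: it can, with the probabilities shown. The efficacy conclusion at T1 is not affected.

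**What to change.** Name the neurofeedback-placebo difference at T2, adjusted for the T0 score of the same measure, as the test of the long-term effect. Obtain it from a mixed model for the T1 and T2 scores with the T0 score as covariate plus group, visit and group x visit, or from an ANCOVA at T2. Keep the three-level group x time interaction as a description of the course over time.

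The cost is a change of wording and a small amount of extra analysis. No new data are needed: T0 scores are collected and already serve as covariate at T1, and mixed modelling is already planned for the sibling comparison.

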### Power calculation

Power calculations used the neurocognitive measures as primary outcome measures. The calculations were done in the statistical program nQuery Advisor [45]. We expect that the neurofeedback will have a medium (d=0.5) to large effect (d=0.8) on neurocognitive functioning as measured at T1 and compared to T0, based on improvements found in children with ADHD who were trained with neurofeedback and on the improvements found in learning-impaired childhood cancer survivors treated with methylphenidate [12,15]. Given an effect size of 0.6 with alpha set at 0.05 (one-sided) and a power of 0.80, a minimum of 35 patients is required in both the neurofeedback group and the placebo group.

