The design of PRISMA has some methodological pitfalls to take into account. Because of time factors and the population, this study might be at risk for losing patients during the treatment phase and during follow-up. With five year survival rates of approximately 65%, some patients may relapse [47], or they may discontinue their participation in the study. We increase comparability by employing three different training modules; however, the training might be less effective than an individualized training. The groups receiving each of the three treatment modules are small. Also, the group of brain tumor patients is heterogeneous, e.g. in terms of tumor diagnosis, tumor location, age at diagnosis, treatment, time since diagnosis, and time since end of treatment. It is well documented that these variables play an important role in neurocognitive outcomes. These heterogeneities may be reflected in our results.

In conclusion, if neurofeedback proves to be effective in improving neurocognitive deficits after treatment for a brain tumor, this would be a valuable addition to the currently available effective interventions for this vulnerable group of pediatric brain tumor survivors.

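### The plan asks whether patient characteristics change the efficacy of neurofeedback, but enters them only as covariates, which cannot answer that question

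*Protocol article*

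**What the plan says.** All of this is in the protocol article, Methods, Statistical analyses, unless stated otherwise.

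- **Aim and start of the method:** "To examine the possible effects of patient characteristics on the efficacy of the neurofeedback, the following variables will be assessed as covariates".
- **Models and variables:** they enter as "covariates in the MANOVA and repeated measures analyses: age at assessment, age at diagnosis, diagnosis, time since diagnosis, and treatment modalities".
- **Only interaction named:** "repeated measures analysis for group (neurofeedback and placebo) x time (T0, T1, and six months follow-up, T2". No product of treatment group with a characteristic is mentioned, and no subgroup comparison.
- **Other use of the word covariate in the section:** baseline adjustment, "T0 data will be included in the model as covariate".
- **Meaning of efficacy:** the last paragraph of the Background says that efficacy is assessed by comparing the effects of neurofeedback with those of placebo feedback.
- **Expected role of the characteristics:** the Discussion lists tumour diagnosis, age at diagnosis, treatment and time since diagnosis among the sources of heterogeneity and adds, "It is well documented that these variables play an important role in neurocognitive outcomes".

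**The concern.** If efficacy is the difference between arms, a characteristic affects efficacy only when that difference changes with it. A covariate entered without a product with group has one coefficient shared by both arms, so it is silent on this.

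Two errors can follow. A characteristic that only predicts outcome gives a significant term, and the stated aim invites a reader to take it as an effect on efficacy. A characteristic that really changes the benefit, but has no average association with outcome, gives nothing. The first is a live possibility here, because the article itself expects most of the listed variables to be prognostic.

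**Working it through.** **1. The plan's own figure.** The Power calculation section gives "Given an effect size of 0.6 with alpha set at 0.05 (one-sided) and a power of 0.80" and concludes that "a minimum of 35 patients is required in both the neurofeedback group and the placebo group". With the normal approximation, n per arm = 2 × (1.645 + 0.842)² / 0.6² = 2 × 6.18 / 0.36 = 34.4, rounded up to 35. The figure reproduces. It concerns the overall group comparison and says nothing about interactions.

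**2. What each term estimates.** Let G be group, X a characteristic, and Y the T1 score.

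- Covariate model: Y = a + b·G + c·T0 + d·X. Neurofeedback minus placebo equals b at every value of X. The test of d asks whether X predicts outcome.
- Interaction model: add e·G·X. The difference is now b + e·X. Only e bears on whether efficacy depends on X.
- Repeated measures model: X x time asks whether X predicts change in both arms taken together. Only G x X x time asks whether the effect of training over time depends on X.

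**3. Size of the mismatch.** Assumptions, because the article gives no values: one outcome, continuous X with SD 1, residual SD 1, 35 per arm, all 70 analysed, two-sided 0.05. The plan's criterion, "A *P*-value <0.05 will be considered significant", does not state sidedness.

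*Purely prognostic X.* X shifts T0 and T1 equally by 0.5 SD per SD, and the benefit is the same for everyone. With T0 in the model and T0–T1 correlation r (given X), the coefficient left for X is 0.5 × (1 − r). The residual SD is √(1 − r²). The variance of X left after T0 is 1 − 0.25/1.25 = 0.8. So SE ≈ √(1 − r²) / √(70 × 0.8).

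| r | coefficient | SE | ratio | approximate rejection | simulated |
|---|---|---|---|---|---|
| 0.5 | 0.25 | 0.116 | 2.16 | 58% | about 54% |
| 0.7 | 0.15 | 0.095 | 1.57 | 35% | about 32% |
| 0.8 | 0.10 | 0.080 | 1.25 | 24% | about 23% |

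The interaction test rejects in 5%, as it should.

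*Pure moderator.* X changes the benefit and has no average association with outcome. The covariate term is significant in about 5–8% of trials. For the interaction, SE ≈ 2 × √(1 − r²) / √70, where r = 0 stands for a model without T0.

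- Benefit changing by 0.3 SD per SD: without T0, 0.3/0.239 = 1.26, so about 24% power (simulated about 22%). With T0 at r = 0.7, 0.3/0.171 = 1.76, so about 42% (simulated about 38%).
- Benefit changing by 0.8 SD per SD: simulated power is 88% without T0, and reaches about 99% with T0.

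*Binary X split 50/50, no T0 adjustment, 4,000 simulated trials.* A prognostic effect of 0.6 SD makes the covariate term significant in 70% and the interaction in 5%. A benefit of 0 in one half and 1.2 SD in the other, with no average association, gives 3% and 69%.

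**4. What the interaction can detect.** For a binary X with share s and no T0 adjustment, SE = √(2/(35s) + 2/(35(1 − s))).

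- s = 0.5: SE = √(2/17.5 + 2/17.5) = 0.478. For 80% two-sided power the interaction must be 0.478 × (1.960 + 0.842) = 1.34 SD. An interaction of 0.6 SD has power Φ(0.6/0.478 − 1.960) = Φ(−0.705) = 0.24.
- s = 0.3: SE = √(2/10.5 + 2/24.5) = 0.522. The corresponding values are 1.46 SD and 0.21.

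**The case against.** **The article does not say main effects.** It says covariates, and a condensed article may leave product terms to the full protocol or the analysis plan. The wording of the aim may even mean that interactions were intended. This stands in part: the reading is the likely one and is not proven. Against it, the section uses the same word for plain T0 adjustment and writes out the one interaction it names. The point also does not rest on a missing detail. The article states a method, and as stated that method does not meet the aim.

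**The prognostic term may seldom be significant.** Diagnosis, age at diagnosis and treatment act before T0, so T0 absorbs much of their effect. This stands. A reader might infer that almost any prognostic factor would show up: with the same 0.5 SD per SD the rate is 97%, but only if T0 is left out. The plan includes T0 in the T1 analysis, so the range of 23–54% is the relevant one.

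**The interaction test is weak.** This also stands. The 88% power needs a change of 0.8 SD per SD, more than the whole planned average effect of 0.6. A moderate moderator would usually be missed. That is a reason to report estimates as exploratory, not to use a term that tests something else.

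**The harm.** A reader might infer that the wrong survivors would be offered training. The documents do not support this. The Study design section offers neurofeedback to placebo patients if effectiveness is shown, with no selection by characteristic. Nor is it certain that the investigators would misread a covariate term, since their Discussion already treats these variables as prognostic.

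**Conclusion.** The point holds as a mismatch between aim and method in a secondary analysis. On the ordinary reading of covariate, the planned terms show which characteristics predict outcome and cannot show which ones change the benefit.

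That conclusion follows from the algebra and needs no assumed effect size. The rates do rest on assumptions: the size of the prognostic or moderating effect, the T0–T1 correlation, a single outcome in place of the MANOVA, and complete data.

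A reader might also infer that the main result is compromised. It is not. The randomised group comparison, its T0 adjustment and the sample size are untouched, and adding prognostic covariates does not bias a randomised comparison.

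**What to change.** Replace the sentence on patient characteristics with text to this effect: *Effect modification will be explored by adding one group x characteristic interaction at a time to the T0-adjusted T1 model, and one group x time x characteristic interaction at a time to the repeated measures model. Estimates with 95% confidence intervals will be reported and regarded as exploratory. Main effects of characteristics serve only as prognostic adjustment of the treatment effect.*

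If effect modification was never the question, it is enough to reword the aim as covariate adjustment.

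The cost is one sentence and a few extra models. The interaction estimates will be imprecise at this sample size, so a non-significant interaction must not be read as evidence that benefit is the same for all. The sample size need not change.

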## Discussion

This article describes the design of the PRISMA study, a randomized controlled trial investigating the efficacy of neurofeedback in pediatric brain tumor survivors with neurocognitive problems. Although neurocognitive problems in pediatric oncology survivors are reported in numerous studies, empirically validated interventions addressing these deficits are scarce. There is growing evidence for neurofeedback as a valuable treatment in different brain disorders [15,21]. Our study is the first to investigate the efficacy of neurofeedback in pediatric brain tumor survivors using a randomized placebo-controlled double-blind trial, comparing neurofeedback to placebo training. By setting an automatically adjusted threshold of feedback as opposed to a manually adjusted threshold, we enabled blinding the trainers; trainers were not required to monitor the brain activity of the patient during the sessions. Furthermore, we ensure the standardization of the neurofeedback treatment by employing carefully instructed research assistants providing the neurofeedback treatment. At the same time we increased the feasibility for the patients, by administering the training at the patients' home or school. In addition, the effects of neurofeedback on neurocognitive and psychosocial functioning are thoroughly investigated by using well-validated paradigms and psychometrically sound questionnaires administered to patient, caregiver and teacher. Lastly, we have included a control group of healthy siblings, to compare performance of the brain tumor survivors to children without a history of a brain tumor.

The design of PRISMA has some methodological pitfalls to take into account. Because of time factors and the population, this study might be at risk for losing patients during the treatment phase and during follow-up. With five year survival rates of approximately 65%, some patients may relapse [47], or they may discontinue their participation in the study. We increase comparability by employing three different training modules; however, the training might be less effective than an individualized training. The groups receiving each of the three treatment modules are small. Also, the group of brain tumor patients is heterogeneous, e.g. in terms of tumor diagnosis, tumor location, age at diagnosis, treatment, time since diagnosis, and time since end of treatment. It is well documented that these variables play an important role in neurocognitive outcomes. These heterogeneities may be reflected in our results.

In conclusion, if neurofeedback proves to be effective in improving neurocognitive deficits after treatment for a brain tumor, this would be a valuable addition to the currently available effective interventions for this vulnerable group of pediatric brain tumor survivors.
